### Hypotheses

Hypotheses for the VA-based study (reflecting a 2-arm trial) are:

Primary

H_1_: Patients with hip and/or knee OA who receive a comprehensive intervention (including both patient-based and provider-based components) will have a larger, clinically relevant improvement in self-reported pain, stiffness and function, as measured by the Western Ontario and McMasters Universities Osteoarthritis Index (WOMAC), compared with usual care.

Secondary

H_2_: The comprehensive OA intervention will result in improvement in objectively assessed physical function (using the Short Physical Performance Test Protocol) when compared to usual care.

H_3_: The comprehensive OA intervention will result in improvement in depressive symptoms (measured with the Patient Health Questionnaire-8 (PHQ-8) [24]) when compared to usual care.

Hypotheses for the Duke-based study (reflecting a 4-arm trial) are:

Primary

H_1_: Compared to usual care, patients with hip and/or knee OA who receive a combined patient-based and provider-based intervention will have a larger improvement in self-reported pain, stiffness and function, as measured by the WOMAC, than either a provider-based or patient-based intervention alone.

H_2_: Patients with hip and/or knee OA who receive either the patient-based OR provider-based intervention will have clinically relevant improvements in WOMAC scores when compared to usual care.

Secondary

H_3_: The patient-based, provider-based, and combined interventions will each result in improvement in objectively assessed physical function (using the Short Physical Performance Test Protocol) when compared to usual care, and the combined intervention will result in the greatest improvement.

H_4_: The patient-based, provider-based, and combined interventions will each result in improvement in depressive symptoms (measured with the PHQ-8 [24]) when compared to usual care, and the combined intervention will result in the greatest improvement.

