### Sample size

For the VA-based study, we will enroll approximately 30 providers (15 per group) with 10 patients per provider (150 per group), for a total sample size of 300. Our goal was to have sufficient sample size to detect a moderate effect size of approximately 0.30 for the primary hypothesis with 80% power and a type-I error rate (alpha) of 0.05. Based on expected mean baseline WOMAC scores of 38 with a standard deviation of 14 (anticipated from our prior pilot work), this effect size translates to a 4.2 point difference at 12-months, which is equivalent to approximately 11% improvement from baseline scores. Sample size calculations were based on methods appropriate for ANCOVA type analyses [56] and adjusted for provider clustering using the method of Donnar & Klar [57]. A correlation of 0.60 between time points was estimated based on our pilot data, and we accounted for a 12% attrition rate. This yielded a final sample size of 150 participants per group.

For the Duke-based study, we will enroll approximately 56 participants across each of 10 clinics, for a total sample size of 560. Our goal was to have sufficient sample size to detect moderate effect size of approximately 0.39 for the primary hypotheses with 80% power and a type-I error rate (alpha) of 0.05. Based on the same pilot data described above, this effect size translates to a 5.5 point difference at 12-months which is equivalent to approximately 15% improvement from baseline scores. For H_1_, this implies that compared to usual care we can detect a 15% greater improvement in WOMAC scores for participants that receive the combined intervention than the improvement in WOMAC scores for participants that receive either the Patient or Provider only at 12-months. For H_2_, this implies we can detect a 15% greater improvement in those that receive either the Patient or Provider intervention as compared to usual care at 12-months. Sample size calculations were based on methods appropriate for ANCOVA type methods, [56] adjusted for clinic clustering using the method of Donnar & Klar [57]. A correlation of 0.60 between time points was estimated based on our pilot data, and we accounted for a 15% attrition rate. This yielded a final sample size of 140 participants per group.

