### Data analyses

The main conclusions drawn from these trials will be based on the pre-specified primary and secondary hypotheses and will be tested with two-sided p-values at the standard 0.05 level. Primary analyses will be conducted on an intent-to-treat basis; participants will be analyzed in the group to which they were assigned, regardless of intervention adherence, using all data up to the 12-months follow-up or last available measurement prior to exclusion or dropout [58]. Statistical analyses will be performed using SAS for Windows (Version 9.2: SAS Institute, Cary, NC) and R (http://www.R-project.org).

For the VA-based study, our primary hypothesis will be tested using a hierarchical linear model with patients nested within providers; baseline, 6- and 12-month values in the response vector will be used to estimate changes in WOMAC scores over time and test the primary hypothesis [59]. A random effect will be included in the model to account for clustering of patients within providers, as the providers are the unit of randomization. Because of the small number of time points, we will apply an unstructured covariance matrix to take into account the within-patient correlation between repeated measures over time. The predictors in the model will include a dummy coded time effect and an indicator variable for the intervention interacting with the time effect. The fixed-effect portion of the model will have the form [60]

(1)$$Y_{\mathrm{ijk}}=\beta_{0}+\beta_{1}*\left(time6\right)+\beta_{2}*\left(time12\right)+\beta_{3}*\left(intervention*time6\right)+\beta_{4}*\left(intervention*time12\right)$$

We will estimate the parameters in the model using the SAS procedure MIXED (Cary, NC). This method handles dropout in a principled manner. However, depending on the type and scope of any missing data, we will also explore multiple imputation as a strategy to use in conjunction with our primary analytic tools [61]. As recommended in the Committee for Proprietary Medicinal Products guidelines, the primary (as well as secondary) analyses will include the race stratification variable as a fixed covariate in the main analytic models. Secondary analyses will be conducted in a similar manner, testing for differences in physical function and depressive symptoms.

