For the Duke-based study, our two primary hypotheses will also be tested using a similar hierarchical linear model, with patients nested within clinic. The predictors in this model will include a dummy coded time effect and separate indicator variables for the Provider and Patient interventions interacting with the time effect. The fixed-effect portion of the model will have the form

(2)$$\begin{array}{l} Y_{\mathrm{ijk}}=\beta_{0}+\beta_{1}*\left(time6\right)+\beta_{2}*\left(time12\right)+\beta_{3}*\left(provider*time6\right)+\beta_{4}*\left(patient*time6\right)\\ +\beta_{5}*\left(provider*patient*time6\right)+\beta_{6}*\left(provider*time12\right)+\beta_{7}*\left(patient*time12\right)\\ +\beta_{8}*\left(provider*patient*time12\right) \end{array}$$

for clinic *i*, patient *j*, at time *k*.

The specific test for H_1_ based on the above model parameterization is testing that *β*_*8*_ equals zero. For H_2_, for the Provider intervention alone compared to usual care at 12-months is a test of *β*_*6*_ equal 0 and for the Patient intervention only it is *β*_*7*_ equal zero*.* The primary (as well as secondary) analyses will include the race and gender stratification variable as a fixed covariate in the main analytic models. Secondary analyses will be conducted in a similar manner, testing for differences in physical function and depressive symptoms.

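### Duke H1 says Combined beats each single intervention, but its stated test, β8 = 0, examines departure from additivity

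*Protocol article*

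**What the plan says.** **Hypothesis.** Protocol article, Hypotheses, Duke H1: relative to usual care, the Combined arm is expected to improve more "than either a provider-based or patient-based intervention alone". H2 is the separate claim that each single intervention beats usual care.

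**Sizing.** The Sample size section plans for a "moderate effect size of approximately 0.39 for the primary hypotheses with 80% power and a type-I error rate (alpha) of 0.05", which it converts to 5.5 WOMAC points. It interprets this for H1 as a 15% greater improvement in Combined than in Patient only or Provider only. For H2 it says that "this implies we can detect a 15% greater improvement in those that receive either the Patient or Provider intervention as compared to usual care". Both are differences between two arms.

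**Model.** Equation (2) in Data analyses uses "separate indicator variables for the Provider and Patient interventions interacting with the time effect", plus their product. It has no arm terms at baseline.

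**Tests.** "The specific test for H_1_ based on the above model parameterization is testing that" β8 equals zero. For H2, the test "for the Provider intervention alone compared to usual care at 12-months is a test of" β6 = 0, and Patient only is tested by β7 = 0. Primary and secondary hypotheses "will be tested with two-sided p-values at the standard 0.05 level".

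**The concern.** The hypothesis and the sample size section describe the same thing: Combined against each single arm. The test describes something else. An interaction coefficient asks whether the two interventions together do more, or less, than the sum of their separate effects. A combined programme can be clearly better than either component without any such excess.

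At stake is the first primary question of the Duke study. If the two effects simply add, the stated test has no power beyond its type I error, although H1 holds. If they are sub-additive and Combined is still better than each component, β8 has the sign opposite to the one that would support H1. The 80% power given for H1 was also not derived for the coefficient that is tested.

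**Working it through.** **1. What each coefficient means.** β6 is assigned to Provider only versus usual care and β7 to Patient only versus usual care. That fixes 0/1 coding. The 12-month differences from usual care are:

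| Arm | Difference from usual care |
|---|---|
| Provider only | β6 |
| Patient only | β7 |
| Combined | β6 + β7 + β8 |

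Hence:
- Combined − Patient only = β6 + β8
- Combined − Provider only = β7 + β8
- β8 = (Combined − Provider only) − (Patient only − usual care)

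H1 is about the first two lines. The stated test is about the third.

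**2. The plan's own figures.** Inputs from Sample size: SD 14, effect size 0.39, correlation 0.60, attrition 15%, 140 per arm, 10 clinics.
- 0.39 × 14 = 5.46 (stated as 5.5), and 5.5/38 = 14.5% (stated as 15%).
- ANCOVA SD = 14 × √(1 − 0.60²) = 11.2.
- Pairwise n = 2 × (11.2 × 2.80/5.46)² ≈ 66.05, so 67 per arm, and 67/0.85 gives 79 enrolled before clustering.
- Completers: 140 × 0.85 = 119, so 140 per arm implies a design effect of 119/66.05 = 1.80. That corresponds to an ICC of about 0.0146 with 56 patients per cluster, or about 0.030 with 28.

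The protocol gives no ICC, so 140 cannot be confirmed, but it is compatible with a pairwise contrast and a modest ICC. The design effect and both ICCs are solved backwards here; they are not planned values.

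**3. The β8 test when H1 is true** (lower WOMAC taken as better).
- *Additive illustration.* β6 = β7 = −5.5 and Combined = −11.0, so β8 = −11.0 + 5.5 + 5.5 = 0. The test rejects in 5% of trials, half of them in the unfavourable direction. Simulation of 10 clinics gave 4.8% to 5.2% for ICC 0 to 0.03.
- *Sub-additive illustration.* β6 = β7 = −5.46 and β8 = +2.73. Combined is still 2.73 points better than each single arm. The test rejects in about 26% to 27% of simulated trials, and in the favourable direction in no more than 0.1%.

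**4. Power for β8 if it is itself 5.5 points.** Both brackets in the expression for β8 are within-clinic differences, because patients are randomised within clinics, so a clinic intercept cancels.
- SE(β8) = 11.2 × √(4/119) = 2.05.
- 5.46/2.05 = 2.66, and Φ(2.66 − 1.96) ≈ 0.76. Using 5.5 also gives 76%.
- Completers needed for 80%: 4 × (11.2 × 2.80/5.46)² ≈ 132 per arm, or 132.1/0.85 ≈ 155 enrolled, against 140.

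**5. Joint power of the two H1 contrasts, additive illustration.** Combined versus Provider only is within clinic. Combined versus Patient only is between clinics (5 against 5), so the ICC matters. The ICC is an assumption, applied to the baseline-adjusted variance:

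| ICC | 8 df | Normal theory |
|---|---|---|
| 0 | 89% | 94% |
| 0.0145 | 80% | 89% |
| 0.03 | 71% | 81% |

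**The case against.** The best defence is that H1 opens with a comparison to usual care and that the authors chose β8 deliberately in a two-factor design, so they may have meant synergy. The wording does not carry that reading: (Combined − usual care) − (single − usual care) = Combined − single, and usual care cancels. To arrive at β8 both single effects must be subtracted, which neither Hypotheses nor Sample size says. What stands is that the intention may have been synergy. Rewording H1 would then be an equally valid repair.

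Three stronger readings are tempting, and the document does not support them.
- *That 5% is the power under the plan's own scenario.* Sample size gives 5.5 points for H1 and for H2 separately and never assumes that both hold together. The additive case is an illustration that H1 and β8 = 0 are compatible.
- *That clustering cuts the power for a 5.5-point β8 to about 51%.* That puts the back-solved design effect of 1.80 on a contrast in which clinic intercepts cancel. It would need clinic-to-clinic variation in the patient intervention's effect, which the protocol does not state.
- *That the repaired joint test must fall below 80%.* That depends on an ICC that is not given and on the degrees of freedom used.

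Nor does the protocol say how a non-significant β8 would be reported. The risk of misreading it is real, but it is not a stated plan.

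**Conclusion.** The mismatch holds: the test named for Duke H1 does not test the hypothesis as stated and as sized. This follows from the algebra of equation (2) and needs no assumption about ICC or effect size.

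The size depends on the truth. Rejection is 5% if the effects add exactly, mostly in the wrong direction if they are sub-additive, and about 76% if the interaction itself is 5.5 points. The last figure rests on SD 14, correlation 0.60, 119 completers per arm and a clinic random intercept only. The stated 80% applies to a pairwise difference and not to β8. If H1 did mean synergy, the shortfall in power would be small (76% against 80%), but the wording of H1 would still be wrong.

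**What to change.** **If H1 stays as worded.** In Data analyses, replace the H1 test by the two 12-month contrasts β6+β8 (Combined versus Patient only) and β7+β8 (Combined versus Provider only). Claim H1 only if both favour Combined at two-sided 0.05; because both are required, this rule needs no alpha adjustment. Report β8 with its confidence interval as a secondary estimate of synergy. In Sample size, restate the H1 power for the joint test and give the assumed ICC and degrees of freedom.

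**If synergy was meant.** Reword H1 in Hypotheses and in Sample size as an interaction hypothesis, keep β8 as its test, and restate the power as about 76% for a 5.5-point interaction.

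Under the first route, use the same contrasts for the claims in H3 and H4 that Combined gives the greatest improvement, since the secondary analyses are to be run in the same way.

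**Cost.** The first route takes a few sentences and two contrast statements in the model already planned, with no new data. Its restated power may fall on either side of 80%, depending on the ICC. The second route costs only rewording and acceptance of the lower power.

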### Economic evaluation

The objectives of the economic evaluation are to: 1) estimate the cost per participant for each study group; 2) estimate the annual OA-related healthcare utilization cost per participant in each group; 3) estimate the effectiveness achieved by each intervention; 4) estimate the incremental cost-effectiveness of each intervention. The Patient intervention cost will consist of labor costs (e.g., counselor training and telephone calls) and equipment and materials costs. The incremental cost incurred for the Provider intervention is primarily due to the additional time needed to collect the information from patients. Based on our prior experience with these assessments, we estimate it will require 15 minutes of time. In clinical practice, these measures would likely be obtained by a nurse. The application of per-minute wage rates will be used to derive this nurse cost.

We expect the interventions may affect two types of healthcare utilization: outpatient visits (including both primary care and specialist visits for OA-related care) and pain medication use. We will collect outpatient visit data primarily from the VA’s Decision Support System administrative dataset and Duke University Medical Center billing data. However, we will also ask patients to report office visits outside of these healthcare systems in follow-up surveys. For the VA –based study, pain medication use will also be extracted from the Decision Support System. We will also ask patients in both VA-based and Duke-based studies to report their pain medication use. For standardization, consistency, and to best approximate cost (rather than charges or reimbursement), we will use Medicare reimbursement rates to monetize outpatient visits. Market prices (e.g., from drugstore.com) will be applied to the reported medications to derive medication cost.

We will use three effectiveness measures to calculate cost effectiveness ratios: WOMAC units (primary outcome), pain-free days (during the prior 30 days), and quality-adjusted life years. The EuroQoL is used to conduct the utility measurements necessary to calculate quality-adjusted life years [62]. Bivariate analyses will be conducted to examine differences in costs and effectiveness among the intervention arms. We will then calculate the incremental cost effectiveness ratio (ICER) of the intervention arms and control group relative to each other. The ICER will be calculated as the difference in the average cost per participant divided by the difference in the average effectiveness per participant between study group.

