## Methods / Design

### Trial design

Both the VA-based and Duke-based studies are randomized controlled trials, but the study designs differ due to variations in the arms being tested. The VA-based study is a cluster randomized controlled trial, in which Primary Care Providers (PCPs) are assigned to one of two study arms: OA Intervention and Usual Care Control. PCPs assigned to the OA Intervention receive the Provider Intervention described below, and their enrolled patients receive the Patient Intervention, also described below.

Figure 1 shows the design of the Duke-based trial, in which clinics are randomized to Provider Intervention vs. Control, then patients within those clinics are assigned to Patient Intervention vs. Control. This results in patients being assigned to one of four study arms: 1.) Patient Intervention Only, 2.) Provider Intervention Only, 3.) Patient Intervention + Provider Intervention and, 4.) Usual Care Control. For both VA and Duke studies, all participants continue with any other usual medical care they receive for OA. After completion of follow-up assessments, participants assigned to the Patient Control condition are given the materials for the Patient Intervention, and clinics / PCPs who were assigned to the Provider Control condition are given the patient-specific recommendations for the Provider Intervention. These studies were reviewed and approved by the Durham VA Medical Center and Duke Institutional Review Boards, respectively.

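### The economic evaluation names bivariate comparisons and simple mean differences, which fit neither the cluster-randomised designs nor the hierarchical, baseline-including model used for the same WOMAC outcome

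*Protocol article*

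**What the plan says.** The Economic evaluation section of the protocol article lists three effectiveness measures: WOMAC units (flagged there as the primary outcome), pain-free days and QALYs. Its stated method of comparison is: "Bivariate analyses will be conducted to examine differences in costs and effectiveness among the intervention arms". The ratio follows: "The ICER will be calculated as the difference in the average cost per participant divided by the difference in the average effectiveness per participant". The section mentions no cluster effect, baseline value or covariate for these comparisons. It does not say whether WOMAC effectiveness is a 12-month score or a change, and it plans no interval for the ICER.

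The Data analyses section treats WOMAC differently. For VA: "A random effect will be included in the model to account for clustering of patients within providers", on the ground that providers are what was randomised, and "baseline, 6- and 12-month values in the response vector will be used to estimate changes in WOMAC scores over time". For Duke, the primary hypotheses "will also be tested using a similar hierarchical linear model, with patients nested within clinic". Both models carry the stratification variables. This approach is extended to physical function and depressive symptoms, but not to costs or economic effectiveness.

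The Duke design has two levels of assignment (Trial design): "clinics are randomized to Provider Intervention vs. Control, then patients within those clinics are assigned to Patient Intervention vs. Control".

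**The concern.** The article names a method, and that method does not fit the design. A bivariate analysis relates arm to outcome and nothing else. The reason given for the random effect in the primary model, that providers were randomised, applies equally to costs, QALYs and pain-free days.

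Two things are at stake. First, tests of cost and effect differences between clusters would reject too often. Second, the WOMAC increment in the ICER denominator could differ from the effect reported in the primary analysis, for no reason other than chance baseline imbalance and a less precise estimator. Cost-effectiveness is announced in the abstract, and the Discussion presents the provider intervention as low in cost, so the results will be read.

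**Working it through.** **Inputs (Sample size section).** VA: effect 0.30 SD (4.2 points), 150 per group, 12% attrition. Duke: effect 0.39 SD (about 5.5 points), 140 per group, 15% attrition. Both: SD 14, correlation 0.60, 80% power, two-sided 5%. No ICC or design effect is stated.

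**1. The plan's sample sizes and the implied design effect.** ANCOVA size per group without clustering: n = 2 × (1.96 + 0.842)² × (1 − 0.60²) / d².
- VA: 2 × 7.85 × 0.64 / 0.09 = 111.6, so 112, or 128 after 12% attrition. The plan has 150.
- Duke: 2 × 7.85 × 0.64 / 0.1521 = 66.1, so 67, or 79 after 15% attrition. The plan has 140.

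The plan's figures are reached only with a clustering allowance. Attributing the whole remaining gap to clustering:
- VA: 150 × 0.88 = 132 completers; 132 / 111.6 = 1.18. With 10 patients per provider, ICC = 0.18 / 9 = 0.02.
- Duke: 140 × 0.85 = 119 completers; 119 / 66.1 = 1.80. ICC is about 0.80 / 27 = 0.03 with 28 patients per arm per clinic, or 0.80 / 55 = 0.015 with 56 per clinic.

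**2. Type I error of a test that ignores clustering.** True level = 2 × [1 − Φ(1.96 / √DE)].
- VA, DE 1.18: 1.96 / 1.086 = 1.80, giving 0.071.
- Duke between clinic arms, DE 1.80: 1.96 / 1.342 = 1.46, giving 0.144. The naive SE is 1 / 1.342 = 0.745 of the correct one, so 25% too small.

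Range over an assumed ICC of 0.01, 0.02 and 0.05:

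| Contrast | Type I error |
|---|---|
| VA, 10 per provider | 6%, 7%, 10% |
| Duke between clinics, 28 per arm per clinic | 8%, 11%, 20% |
| Duke between clinics, 56 per clinic | 12%, 18%, 31% |

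**3. Which Duke contrasts are affected.** Four of the six pairwise arm contrasts compare different clinics: Provider Only vs usual care, Combined vs usual care, Combined vs Patient Only, and Patient Only vs Provider Only. The other two (Patient Only vs usual care, Combined vs Provider Only) compare patients within the same clinics. For these the true variance is (1 − ICC) times the naive one, so a naive test is slightly conservative.

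**4. Precision lost by leaving out baseline.** Variance relative to ANCOVA:
- Raw 12-month score: 1 / (1 − 0.36) = 1.56.
- Change score: 2 × (1 − 0.60) / 0.64 = 1.25.

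**5. Chance divergence from the primary estimate.** A raw 12-month difference departs from the baseline-adjusted one by 0.60 × the baseline difference.
- VA: SD = 0.6 × 14 × √(2/150) = 0.97 points, against a target of 4.2.
- Duke: SD = 0.6 × 14 × √(2/140) = 1.00 points, against 5.5. If the 1.80 design effect also holds at baseline, 1.00 × 1.342 is about 1.35 for between-clinic contrasts.
- For a change score the multiplier is 0.40, giving 0.4 × 14 × √(2/150) = 0.65 and 0.4 × 14 × √(2/140) = 0.67.

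Illustration for the Duke ICER: a one-SD divergence of 1.35 moves a denominator of 5.5 to 4.15 or 6.85. At fixed incremental cost the ICER changes by 5.5/4.15 − 1 = +33% or 5.5/6.85 − 1 = −20%.

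**The case against.** Several stronger readings are tempting and do not stand.

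- *The ICER's error bars will be too narrow.* No interval or standard error is planned for the ICER in this article, and a condensed article may leave that to the full plan. The anticonservatism concerns the bivariate tests only.
- *Everything becomes too narrow.* Omitting baseline widens standard errors. For VA the naive unadjusted SE is 14 × √(2/132) = 1.72. Clustering raises it to 1.72 × 1.086 = 1.87, and baseline adjustment brings that to 1.87 × 0.8 = 1.50. The naive SE is thus too small for its own estimator, yet larger than that of the primary model.
- *The trial will report two different WOMAC effects.* Under randomisation the raw and adjusted differences have the same expectation. They can differ, typically by about a point. Duke clinics are also randomised in matched pairs, which should limit imbalance.
- *The economic analysis loses its 80% power.* No economic hypothesis is stated and no power was claimed. The economic objectives are all to estimate, and the rule that hypotheses "will be tested with two-sided p-values at the standard 0.05 level" is tied to the primary and secondary ones.

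It is also fair to say that the ICER sentence is the standard definition of the ratio and could be filled with model-based means, and that average effectiveness could be a mean change. This softens the baseline part. It does not remove the mismatch, because the comparison sentence explicitly names a bivariate method for cluster-randomised data.

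**Conclusion.** The concern holds in a limited form. The stated economic method does not match the clustered designs or the article's own model for WOMAC. Bivariate tests of VA contrasts and Duke between-clinic contrasts would have a true type I error of about 7% and 14% at the back-solved design effects; Duke within-clinic contrasts are not inflated. The WOMAC increment can diverge from the primary estimate by chance with an SD of about 1 point (about 1.35 for Duke between-clinic contrasts under the same assumption), and its variance is 1.56 or 1.25 times that of the adjusted estimate, depending on whether a raw 12-month or a change score is used.

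The type I figures rest on design effects inferred from the sample sizes and on normal approximations. They also carry a WOMAC-based ICC over to costs and QALYs, where it may be different. The primary and secondary hypothesis tests are untouched, so this is a correction to a supporting analysis.

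**What to change.** Replace the sentence on bivariate analyses in the Economic evaluation section.

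- **WOMAC:** use the relevant 12-month contrast from the primary mixed model as the incremental effect, so that one estimate serves both purposes.
- **Costs, QALYs and pain-free days:** estimate arm differences with a provider (VA) or clinic (Duke) random effect, adjusting for the baseline value where one is collected.
- **Any ICER interval:** obtain it by resampling clusters, not patients alone.

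The cost is a few extra model fits and, if an interval is reported, a bootstrap program. No new data are needed.
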